#### Data Analysis

The student's *t*-test or Wilcoxon rank-sum test was used to compare the continuous variables and the chi-square test or Fisher exact test was used as appropriate for categorical variables for the comparison of patients with or without infections in both datasets.

The risk score was developed using a backward stepwise logistic regression model. All candidate predictors were included in the development of the risk score, and to avoid overfitting data and select the best subset of risk factors, a bootstrap method was used. For missing data, 10 multiple imputations were performed using the SAS MI procedure, and 100 bootstrap repeats were conducted for each imputation. Variables selected in at least 90% of 1,000 bootstrap repeats were included in the final model. The risk score was developed for each imputed data via using the selected variables and the SAS MIANALYZE procedure was used to combine the results of the analyses. For this risk score, the scoring method was analogous to that of Sullivan et al. (21) and was used based on the developed risk score. For the scoring purpose, continuous variables were categorized into groups regarding the clinical significance. The risk score of post-AMI consisted of four levels (low-risk, moderate-risk, high-risk, and very high-risk) in order to enhance the clinical utility.

Both discriminatory accuracies assessed by the C-statistic and calibration measured by the Hosmer-Lemeshow χ^2^ statistic and calibration plot were used to evaluate the predictive accuracy of the risk score. The bootstrap method with 1,000 bootstrapped replications was used to perform an internal cross-validation of the risk score. The average of the C-statistic was reported. In addition, external validation and subgroup validation (older, gender, diabetes, anemia, and chronic kidney disease) of the risk score model was conducted to assess the stability of the model. The risk score was also validated in patients with NSTE-ACS undergoing PCI, and the area under curve (AUC) of this risk score was compared to the previous scoring systems (6, 7). Furthermore, comparison of the area under the receiver operating characteristic (ROC) curve was according to the nonparametric approach of DeLong et al. (22). To evaluate the clinical utility of this risk score, decision curve analysis was introduced and the risk score with a higher net benefit indicated a better clinical effect (23).

All statistical analyses were performed using SAS (version 9.4, SAS Institute, 210 Cary, North Carolina, USA).

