### Laboratory Testing

Blood samples were obtained routinely and tested for electrolytes, white blood cell count, hemoglobin, cardiac enzymes, serum creatinine, blood lipids, serum albumin, total bilirubin, estimated glomerular filtration rate (eGFR) that was evaluated using the modified Modification of Diet in Renal Disease (MDRD) equation for Chinese people (17) and other routine laboratory parameters with 24 h after admission, while the medical history, the vital signs including body temperature, pulse rate, respiration rate and blood pressure, and Killip classification were also recorded at the same time.

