### Data Collection and Missing Data

Clinical data including patient demographics, diagnosis, medical histories, clinical and laboratory characteristics, medication treatment, procedural details and main outcomes were obtained through review of electronic medical records. The principal data, such as clinical outcomes, were collected by two investigators independently, and inconsistent data were verified by a third investigator.

Variables were included as candidates for this risk score after removing variables with ≥ 10% missing values (Table 1), and for those with incomplete data, we assumed that patients with the missing data ≤ 5% occurred at random depending on the clinical variables and used multiple imputations. This risk score model was developed based on imputed complete cases.

**Table 1 T1:** Observations and endpoints.

**Category**	**Method and materials**	**Observation and examination items**
Demographic characteristics	Interview	Age, sex and smoking status.
STEMI	Medical examination and interview	Onset of STEMI, date of hospitalization, description of treatment.
History of present illness/previous history/therapies	Interview	Previous history of cardiovascular and cardiovascular risk-related diseases and history of treatment (Hypertension, MI, CABG, COPD, AF, stroke, PCI, sudden cardiac arrest, thrombolysis, pericardial effusion, PCI lesion).
Physical findings	Medical examination	SBP, DBP, heart rate and Killip class.
Family history	Interview	Coronary artery diseases, hypercholesterolaemia and ischaemic cerebral infarction in relatives to the second degree of kinship.
Hematological and biochemical examinations	Serum and urine	The following parameters will be measured from blood acquired within 24 h after admission: WBC, eGFR, creatinine, albumin, hemoglobin, TG, TC, total bilirubin, direct bilirubin, LDL, HDL, ALT, CO_2_ combining power, Urine PH.
Heart function	Echocardiography	LVEF, LVDd, LVDs.
Medication during hospital stay	Electronic medical record	Statins, Warfarin, Tirofiban, ARB, CCB, ACEI, β-blockers, insulin, metformin, PPI, diuretics and nitrates.
Procedural characteristics	Electronic medical record	PCI approach, multi-lesion, contrast volume, number of stents and total length of stents.

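### The 90% bootstrap-inclusion rule is applied variable by variable to a list holding both creatinine and the eGFR computed from it, so a real renal signal can split its selections and be dropped

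*Protocol article*

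**What the plan says.** In the protocol article, Data Analysis: "The risk score was developed using a backward stepwise logistic regression model". On what enters, the same paragraph states: "All candidate predictors were included in the development of the risk score". Ten imputations are made, "100 bootstrap repeats were conducted for each imputation", and the retention rule is "Variables selected in at least 90% of 1,000 bootstrap repeats were included in the final model". The threshold is therefore applied to each variable on its own.

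Data Collection and Missing Data gives one filter on the candidates, removal of variables with 10% or more missing values, and points to Table 1. The laboratory row of that table includes "WBC, eGFR, creatinine, albumin, hemoglobin, TG, TC, total bilirubin, direct bilirubin, LDL, HDL, ALT", and the heart-function row reads "LVEF, LVDd, LVDs". Table 1 also lists SBP with DBP, and number with total length of stents. Age and sex are there too. Laboratory Testing describes the "estimated glomerular filtration rate (eGFR) that was evaluated using the modified Modification of Diet in Renal Disease (MDRD) equation", so eGFR is a calculated function of creatinine, not a separate measurement.

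The article describes no grouping of overlapping variables, no correlation check and no prior choice within a pair.

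**The concern.** When two candidates carry nearly the same information, backward elimination tends to keep one and discard the other, and which one survives varies from resample to resample. The selections for a single signal are then shared between two names. A threshold applied to each name separately can reject both, even though the signal is present in almost every resample.

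The article says the bootstrap is there to avoid overfitting and to find the best subset of risk factors. If renal function dropped out for this reason, that would reflect its being entered twice and not a lack of predictive value. The resulting score is then to be compared with two earlier scores, one of which (ACEF, described in the Introduction) is built on age, creatinine and LVEF.

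**Working it through.** **The plan's own figures.** 8 factors × 10 events per variable = 80 infections; 80 / 0.10 = 800 patients. 10 imputations × 100 bootstraps = 1,000 repeats. Both reproduce.

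**The mechanism.** Let f1 and f2 be the shares of repeats that select each member of a pair, and f12 the share that selects both. The share selecting at least one is f1 + f2 − f12. The rule requires f1 ≥ 0.90 or f2 ≥ 0.90 and ignores the union. If the two are rarely kept together (f12 near 0) and the union is near 1, then f1 + f2 is near 1, and one member passes only if the other is chosen in about 10% of repeats or fewer.

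**Check 1: a generic correlated pair.** Taken from the article: 10% incidence, N = 800, backward elimination, the 90% rule. Assumed, because the article gives none: p-to-stay 0.05; log-OR 0.5, 0.7 or 1.0 per SD; pair correlation r of 0.7 to 0.95; a second sample size of N = 2,000; three further independent candidates, one of them predictive. There were 160 datasets of 100 bootstraps per scenario, so the Monte Carlo SE is at most √(0.25/160) ≈ 4 points.

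An example with N = 800, both members measuring one latent factor, r = 0.95, log-OR 0.7: mean f1 = 0.52, f2 = 0.52, union 0.99, hence f12 ≈ 0.52 + 0.52 − 0.99 = 0.05. Neither member reached 90% in 79% of datasets. One member offered alone passed in 96%.

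Share of datasets in which neither member reaches 90%:

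| Truth | r | N = 800 | N = 2,000 |
|---|---|---|---|
| Both measure the same factor | 0.9–0.95 | 75–81% | 73–76%, but 41% at r = 0.9 with log-OR 1.0 |
| Both measure the same factor | 0.7–0.8 | 37–82% | 0–68% |
| Only one is the true predictor | 0.95 | 78 / 64 / 48% | 55 / 42 / 20% |
| Only one is the true predictor | 0.9 | 70 / 44 / 26% | 39 / 17 / 1% |
| Only one is the true predictor | 0.7–0.8 | 1–60% | 0–12% |

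(Three figures in a cell are for log-OR 0.5 / 0.7 / 1.0.)

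One or the other member was selected in 92–100% of bootstraps in every scenario. The loss exceeds 50% in 23 of 48 scenarios: 15 of the 24 with r ≥ 0.9, and 8 of the other 24.

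**How much is the cut-off alone.** At N = 800 and log-OR 0.5, a member offered alone still fails the 90% rule in 21% of datasets (one true predictor) or 23–44% (shared factor). At N = 2,000 it passes in 99–100%.

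**Check 2: eGFR computed from creatinine, no correlation imposed.** eGFR was generated from creatinine, age and sex, with age and sex also candidates. Assumed: an MDRD-type form with creatinine exponent −1.2, log-creatinine SD 0.25 or 0.40, log-OR 0.5 or 0.7 per SD, p-to-stay 0.05, and 80 datasets × 60 bootstraps (SE up to √(0.25/80) ≈ 6 points). The true risk was linear in log creatinine, in eGFR or in raw creatinine. The resulting correlation was −0.80 to −0.88.

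- N = 800: neither passes in 43–76% of datasets, above 50% in 10 of 12 scenarios; one or the other is selected in 90–100% of bootstraps; eGFR alone passes in 59–97%.
- N = 2,000: neither passes in 3–71%, above 50% in 3 of 12; eGFR alone passes in 95–100%.

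A separate run of the same kind gave 47–78% at N = 800 and 13–75% at N = 2,000, with eGFR alone passing in 67–100%. Across both runs the ranges are 43–78% and 3–75%.

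**The case against.** A reader might infer that the rule will usually discard real predictors, strip out whole domains such as blood pressure or ventricular function, and cost the score discrimination. The documents do not support that.

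- The loss is not general. It exceeds 50% in fewer than half of the generic scenarios and falls to 1% when one member is clearly better, the effect is strong and there are 2,000 patients.
- A computational link is documented only for eGFR and creatinine. No correlation is given for SBP/DBP, LVEF/LVDd/LVDs, TC/LDL or the stent measures, so a high value cannot be carried over to them.
- No C-statistic was computed with and without the lost variable; correlated variables that remain may carry some of the signal. The planned validation and decision curves could reveal poor performance, though they would not repair selection.
- No inclusion frequencies are reported, so no actual loss is shown. The Introduction already announces seven predictors, unnamed, against a ceiling of eight, which gives no sign that the rule emptied the model.
- A strict threshold is a legitimate choice for parsimony, and part of the loss at 80 events belongs to it.

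All of these stand as limits on size. The further objection, that an article leaves collinearity screening to a fuller plan and that Table 1 is a list of observations, carries less weight. The text states that all candidates entered, names its one filter and cites Table 1 when it does so. This is a stated rule that works badly on a stated list. A fuller plan might still deal with it.

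**Conclusion.** The concern holds in limited form. As written, the 90% rule can drop a real renal signal because creatinine and eGFR are both candidates. With the assumptions of the second check, that happens in roughly half to three quarters of datasets at the planned 800 patients and 80 infections. At 2,000 patients the range of about 3–75% is too wide to call the loss typical. It is rarer when one member is clearly the better predictor or the correlation is lower.

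The effect sizes, p-to-stay, creatinine distribution and larger sample size are assumptions. The size for the other overlapping sets, total and direct bilirubin included, depends on correlations the article does not give, and the consequence for discrimination is unknown. The point deserves a change because the remedy is cheap, not because damage has been shown.

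**What to change.** Before selection, fix one member of each near-duplicate set: at least creatinine or eGFR, and one of the two bilirubins. Choose on clinical grounds and completeness, without reference to the outcome, and then apply the 90% rule unchanged. Alternatively, count inclusion jointly for the set and carry one member forward when the set reaches 90%.

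The past tense of Data Analysis and the announced seven predictors suggest that selection may already have been run. If so, report the pairwise and joint inclusion frequencies for each overlapping set, and rerun the selection with one member per set as a sensitivity analysis.

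No new data are needed, and choosing one member per set shortens the candidate list. The cost is a rerun if selection is complete, and that the omitted member can no longer contribute any separate information.

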### Study Population

STEMI was defined as the manifestation of typical chest pain and concomitant symptoms for ≥ 30 min but <12 h, with ST-segment elevation ≥ 1 mm in ≥ 2 continuous leads or new or undetermined duration of left branch bundle block accompanying with ≥ 2 times increase in troponin I or T (15).

The inclusion criteria were as follows: (a) age ≥ 18 years; patients with STEMI undergoing PCI, admitted to the cardiac intensive care unit; (b) patients could understand and agree with informed consent.

The exclusion criteria were as follows: (a) patients diagnosed with infection or treated with antibiotics prior to admission; (b) patients with tumor or chronic inflammatory diseases; (c) patients on hemodialysis at admission; (d) patients undergoing emergency cardiac surgery; (e) patients died within 24 h after admission; (f) readmission to hospital; and (g) patients with missing variables that are needed to calculate the risk scores.

Eligible patients were consecutively enrolled between January 1st 2010 and May 31st 2016, which were served as a development cohort. In accordance with the inclusion and exclusion criteria, patients enrolled from June 1st 2016 to May 31st 2018, with complete data regarding risk factors identified in the development cohort, will be served as a validation cohort. Furthermore, the patients screened according to the criteria in other centers will be enrolled for external validation.

To extend the application, this risk score will also be validated in our previous study including patients diagnosed with non-ST-elevation acute coronary syndrome (NSTE-ACS) following PCI according to the same exclusion criteria (16). This retrospective cohort study was designed to evaluate the association between parenteral anticoagulation therapy and clinical outcomes in patients mentioned above. Patients with principal discharge diagnosis of non-ST elevation myocardial infarction (NSTEMI) or unstable angina (UA) and underwent PCI during the index hospital stay were included. And patients with elevated cardiac biomarker and without new ST-elevation on ECG prior to index PCI were classified as NSTEMI while those were classified as UA if there were no positive cardiac biomarker findings and without new ST-elevation on ECG prior to index PCI (16).

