### Statistical Analysis

#### Sample Size Consideration

A rule of thumb, namely, that the event per variable (EPV) was 10 or greater under this circumstance was applied for the sample size determination. Given no more than 8 risk factors in developing a predictive model, thus at least 80 infections were needed. According to the previous studies (3), the incidence of infection was 10%, and at least 800 patients should be finally included.

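### The Hosmer-Lemeshow statistic is the only calibration number named beside the plot; calibration intercept (or O/E ratio) and slope with confidence intervals should be added for the validation cohorts

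*Protocol article*

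**What the plan says.** The Data Analysis section of the Protocol article judges predictive accuracy by the C-statistic for discrimination and by "calibration measured by the Hosmer-Lemeshow χ^2^ statistic and calibration plot". It names no calibration intercept, O/E ratio or slope, and no confidence interval for calibration. For the bootstrap internal validation the only output named is the C-statistic: "The average of the C-statistic was reported". Decision curve analysis is also planned.

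The score is to be carried to three further sets of patients: the later cohort, "patients enrolled from June 1st 2016 to May 31st 2018, with complete data regarding risk factors identified in the development cohort"; other hospitals, where "the patients screened according to the criteria in other centers will be enrolled for external validation"; and an earlier NSTE-ACS cohort. There is also "subgroup validation (older, gender, diabetes, anemia, and chronic kidney disease"). None of these has a stated size. The only size given is the minimum in Sample Size Consideration: "Given no more than 8 risk factors in developing a predictive model, thus at least 80 infections were needed", then "the incidence of infection was 10%, and at least 800 patients should be finally included".

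**The concern.** The score is meant to give a patient's own infection risk and to sort patients into four levels. That use depends on the absolute risks being right, as well as on the ranking. Two kinds of error are plausible in this design:

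- **Wrong mean risk.** The score moves to a later period, other hospitals and a different diagnosis, where infection may be more or less common.
- **Slope below 1.** Backward selection at about 10 events per variable can produce predictions that are too extreme.

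The Hosmer-Lemeshow statistic sums squared discrepancies over risk groups into one chi-square. It discards the sign of the error, estimates nothing and carries no interval. If it also has low power at realistic sizes, a reassuring value says little. The plot helps, but it gives no number that can be compared across cohorts.

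**Working it through.** **1. The plan's own figure.** Events per variable 10 and at most 8 factors (Sample Size Consideration) give 10 × 8 = 80 infections. At 10% incidence, 80 / 0.10 = 800 patients. The stated minimum reproduces.

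**2. Inputs that are assumptions.** C-statistic 0.75 (0.70 and 0.80 also tried); normally distributed linear predictor LP; 10% mean predicted risk; 10 risk groups; 200 to 3,000 patients; and the degrees of miscalibration tested.

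**3. Measures compared, at two-sided 5%, in data independent of development.**

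- Hosmer-Lemeshow: Σ (O_g − E_g)² / [E_g(1 − E_g/n_g)] over 10 groups, 10 degrees of freedom.
- Intercept: α in logit P = α + LP; target 0.
- Slope: β in logit P = α + β·LP; target 1.
- Joint: likelihood-ratio test of α = 0 and β = 1, 2 degrees of freedom.

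**4. Chance of flagging the error, 800 patients, C = 0.75.** There were 5,000 replicates, so the Monte Carlo standard error is at most √(0.25/5000) = 0.7 percentage points.

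| Truth | Hosmer-Lemeshow | Intercept or slope interval | Joint test |
|---|---|---|---|
| Perfect calibration | 5.7% | 9.8% (either of the two) | 5.3% |
| O/E 0.80 | 9% | 52% (intercept) | 44% |
| O/E 1.25 | 44% | 68% (intercept) | 56% |
| Slope 0.8 | 22% | 33% (slope) | 25% |
| Slope 0.7 | 40% | 64% (slope) | 53% |

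A repeat of the simulation agreed within about two points. The direction was the same at C = 0.70 and 0.80.

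**5. Other sizes, C = 0.75, Hosmer-Lemeshow v intercept.**

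| Patients | O/E 0.80 | O/E 1.25 |
|---|---|---|
| 200 | 4% v 16% | 23% v 26% |
| 300 | 3% v 21% | 25% v 33% |
| 1,500 | 27% v 81% | 68% v 90% |
| 3,000 | 69% v 99% | 94% v 99% |

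For slope error at 200 patients, Hosmer-Lemeshow v the slope test is 15% v 13% (slope 0.8) and 22% v 23% (slope 0.7). At 3,000 it is 53% v 83% and 87% v 99%.

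**6. What an interval would show.** Under perfect calibration the standard error of the slope is about 0.14 at 800 patients, so an estimate of 1 has an interval of 1 ± 1.96 × 0.14, or about 0.73 to 1.27. At 200 patients it is about 0.29, giving about 0.43 to 1.57. The second interval openly says that the cohort cannot settle the question; a non-significant chi-square does not.

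**7. Where Hosmer-Lemeshow does better.** With curved miscalibration built so that the intercept is 0 and the slope 1, at 800 patients it flagged 12% to 52%, against 4% to 9% for the joint test. It also catches gross mean error: O/E 1.5 at 800 patients is flagged 96% of the time.

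**The case against.** The strongest reply is that the plan also fixes a calibration plot, which shows the direction and rough size of error, and a decision curve analysis, which is affected by miscalibration if it is run on predicted risks. This is also a condensed article that commits to TRIPOD reporting, so a fuller list of estimates may sit in an analysis plan not shown. The first part stands: the plan is not blind to miscalibration. The second does not remove the point, because the article does choose its numerical measure, and that choice can be improved.

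Several stronger readings are tempting but not supported:

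- *That a non-significant result will be read as proof of calibration.* The article sets no threshold and states no such rule.
- *That the weakness is established at this study's size.* The 800 is a minimum derived for model development. Spreading it evenly over the calendar would put the later cohort at 800 × 24/101 ≈ 190 patients if 800 covers both periods, or 800 × 24/77 ≈ 249 if it covers development only. Both are assumptions and floors.
- *That intercept and slope rescue small cohorts or subgroups.* Near 200 patients they detect slope error and under-prediction hardly better.
- *That Hosmer-Lemeshow should be dropped.* Step 7 of the working argues against it.
- *That the C-statistic alone will judge stability in subgroups, and will mislead through a restricted range.* The article does not say it stands alone, and it does not name the score's components.

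One further limit stands. The simulation uses a continuous predictor in 10 groups, whereas the product is a points score built from categorised variables. The percentages therefore show the ordering and approximate size of the gain and are not forecasts for this score.

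**Conclusion.** The point holds in a limited form. Hosmer-Lemeshow is the only calibration number named, and it reports no size, direction or precision. At 800 patients, 10% incidence and C about 0.75, it misses 56% to 91% of mean errors of 20% to 25%, and 60% to 78% of slopes of 0.7 to 0.8. Intercept or slope estimates from the same data detect more of each. With false alarms held near 5% by the joint test, the gain remains clear for mean error and slope 0.7 but is small for slope 0.8. It narrows in large cohorts. Near 200 patients it almost disappears except for over-prediction, and the main benefit becomes an honest interval.

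The gain applies to the validation cohorts and to bootstrap-corrected results. In the development data the fitted logistic model has intercept 0 and slope 1 by construction. All percentages rest on the assumptions in step 2 of the working, because the article gives no validation size. This is a worthwhile improvement to the plan; it does not invalidate the study.

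**What to change.** In Data Analysis:

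- Name the calibration intercept (or O/E ratio) and the calibration slope, each with a 95% confidence interval, as the primary numerical calibration measures for the June 2016 to May 2018 cohort, the other centres and the NSTE-ACS cohort.
- Report a bootstrap-corrected calibration slope for the development cohort, from the 1,000 replications already planned.
- Read these as estimates. If a test is wanted, use the joint two-degree-of-freedom test, because two separate intervals used as tests give about 10% false alarms.
- Keep the calibration plot, and keep Hosmer-Lemeshow as supplementary for its sensitivity to curvature. State its number of groups and degrees of freedom: in the simulation at 800 patients, using 8 instead of 10 on independent data raised its false-alarm rate to about 11%.

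The cost is a change of wording and two extra estimates per cohort, from a logistic model with one covariate (the log-odds of the predicted risk). No new data or patients are needed.

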Given these data, this research protocol aims to develop and validate a practical risk score to identify the risk of post-AMI infection in patients with STEMI undergoing PCI. And this new risk score based on seven simple independent predictors would be divided into four levels according to the corresponding marks (low-, moderate-, high-, and very high-risk groups) to improve the clinical utility. Therefore, the present risk score could be easily applicable in clinical practice for identifying patients at high-risk of infection and in-hospital outcomes in patients with STEMI undergoing PCI and may help clinical decision-making allowing for timely measures to improve clinical outcomes.

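### The internally validated C-statistic is a plain bootstrap average with no optimism correction described, so it is likely to be modestly too high

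*Protocol article*

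**What the plan says.** All of this is in the protocol article.

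- **Internal validation (Data Analysis).** A bootstrap with 1,000 replications serves as an "internal cross-validation of the risk score. The average of the C-statistic was reported". Neither of these two sentences says in which patients each replicate's C is computed. Optimism, shrinkage or a corrected C is not mentioned anywhere in the article.
- **Model building (Data Analysis).** "The risk score was developed using a backward stepwise logistic regression model", and "All candidate predictors were included in the development of the risk score". The retention rule is: "Variables selected in at least 90% of 1,000 bootstrap repeats were included in the final model". Continuous variables are then grouped by clinical significance and converted to points.
- **Size of the model.** The Introduction describes "this new risk score based on seven simple independent predictors". Sample Size Consideration states: "Given no more than 8 risk factors in developing a predictive model, thus at least 80 infections were needed", and reaches at least 800 patients at 10% incidence.
- **Other validation (Study Population, Data Analysis).** The score is also to be validated in patients enrolled from June 2016 to May 2018, in other centres, and in NSTE-ACS patients.

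**The concern.** A model looks better in the data that produced it than in new patients. Bootstrap internal validation estimates that excess and removes it. For each replicate, one takes the C of the bootstrap model in its own resample minus the C of the same model in the original data, averages this difference over replicates, and subtracts it from the apparent C.

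Averaging the C-statistics leaves the subtraction out. If the finished score is re-evaluated in resamples, the average returns the apparent C. If the model is refitted and scored in the same resample, the average carries the optimism of the development data and some from the resample as well. Either way the reader would see a figure labelled as validated that has not been corrected.

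Selection makes this more than a formality. Many candidates are screened against a number of infections that was sized for eight predictors.

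**Working it through.** **1. The plan's own figure.** Events = 10 per variable × 8 variables = 80. Patients = 80 / 0.10 = 800. Both reproduce. The article gives no C-statistic and no optimism figure to check.

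**2. Candidates against events.** Counting Table 1 by row: 3 demographic + 11 history + 4 physical + 3 family history + 14 laboratory + 3 echocardiographic + 12 medication + 5 procedural = 55 items, before removal of variables with 10% or more missing. At the minimum size, 80 / 55 ≈ 1.5 events per candidate.

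**3. Assumptions for the simulations.** Independent normal predictors, 10% infections, p<0.05 to stay in the model, no missing data, no rounding to points, true-model C between 0.73 and 0.87. True C is taken in 60,000 new patients. There are 60 bootstraps per dataset and few datasets per setting (25 in step 5, 40 in step 4), so the third decimal is approximate.

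**4. Seven fixed predictors, no selection.** Average C refitted and scored in the same resample, minus:

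| N | apparent C | optimism-corrected C |
|---|---|---|
| 800 | 0.006 to 0.013 | 0.016 to 0.037 |
| 1,600 | 0.002 to 0.005 | 0.008 to 0.015 |
| 2,500 | 0.002 to 0.004 | 0.006 to 0.010 |

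The average never fell below the apparent C.

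**5. With the plan's 90% inclusion rule.** Excess = average in-resample C of the refitted final predictors − true C.

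| N | candidates | mean number kept | average C | true C | excess |
|---|---|---|---|---|---|
| 800 | 30 | 4.8 | 0.792 | 0.753 | 0.040 |
| 800 | 30 | 6.6 | 0.875 | 0.854 | 0.021 |
| 800 | 50 | 2.8 | 0.735 | 0.689 | 0.046 |
| 800 | 50 | 4.4 | 0.811 | 0.780 | 0.031 |
| 800 | 50 | 2.5 | 0.732 | 0.706 | 0.027 |
| 1,600 | 50 | 6.9 | 0.809 | 0.798 | 0.010 |
| 1,600 | 50 | 5.6 | 0.794 | 0.777 | 0.018 |
| 2,500 | 50 | 6.7 | 0.746 | 0.722 | 0.024 |

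(Excess is computed before rounding.) A separate simulation at N = 800 with 55 candidates (87 datasets in which at least one variable was kept) gave apparent 0.668, average 0.668 and true 0.620: an excess of 0.668 − 0.620 = 0.048.

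**6. Other readings of the sentence, same N = 800 runs.**
- Finished score re-evaluated in resamples: within about 0.001 of the apparent C (for example 0.787 against 0.787, and 0.732 against 0.731).
- Bootstrap models tested in the original data: still 0.011 to 0.039 above the true C.
- Out-of-bag patients only: not simulated. This would not be optimistic in the way described.

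**7. Does the correction need selection inside it?** At N = 800, correcting only for refitting the final predictors left 0.007 to 0.035 of excess. Repeating plain backward elimination in each replicate, without the 90% threshold, gave values 0.004 to 0.029 below the true C across all eight settings (for example 0.742 against 0.753). That shortcut over-corrects, because it subtracts the optimism of a larger model than the one reported. The 90% rule nested inside each replicate was not simulated.

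**The case against.** The strongest reply is that the sentence does not say where each C is evaluated. Calling the procedure a cross-validation is compatible with testing on patients left out of the resample, and a condensed article may leave that detail to an unseen analysis plan. This stands in part: overstatement is likely, not certain. But the article does fix the reported quantity as an average, and nothing in it points to left-out patients.

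The simulations also lean on a floor. 800 is a minimum, development enrolment runs for more than six years, the actual number of patients is not given, and the candidate list shrinks once variables with much missing data are dropped. The runs that kept close to seven predictors gave only 0.010 to 0.024. This stands, and is why the size is given as a range.

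A reader might infer three stronger things that the documents do not support.

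- *An overstatement of 0.05 to 0.10.* Gaps of that order arise mainly when selection is repeated in every replicate and the in-sample C values are averaged (0.041 to 0.154 at N = 800 in these runs), or when the 90% rule is ignored. The article states neither.
- *A false win over published scores with C of 0.697, 0.708 and 0.727.* The Discussion cites these as background on infection after cardiac surgery. The planned AUC comparison is with the ACEF and CACS scores, appears alongside the NSTE-ACS validation, and is not said to use development data.
- *That all evidence of discrimination is compromised.* The later cohort, other centres and NSTE-ACS patients carry no fitting optimism from the development sample.

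**Conclusion.** The point holds for the internal-validation figure. As worded, the plan reports a quantity that sits at or slightly above the apparent C and removes no optimism, so internally validated discrimination is likely to be overstated. Under the assumptions in the working, the excess is roughly 0.02 to 0.05 at 800 patients and about 0.01 to 0.025 at 1,600 to 2,500. The true size depends on the number of patients, infections and usable candidates, none of which the article gives. The planned validation outside the development data limits the harm. This is a correction worth making, and it does not undermine the study as a whole.

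**What to change.** Replace the sentence on the average C-statistic with:

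> The optimism-corrected C-statistic will be reported: the apparent C minus the mean, over bootstrap replicates, of (C of the bootstrap model in its own bootstrap sample minus C of that same model in the original sample). Variable selection and point assignment are repeated in each replicate, and the pre-set clinical categories are held fixed.

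The selection repeated in each replicate should be the plan's own rule, including the 90% threshold, because plain backward elimination over-corrected in the working. The categories stay fixed because the plan sets them on clinical grounds and not from the data.

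The cost is one sentence, no new patients or data, a somewhat lower reported C, and computing time. Nesting the full rule at the plan's counts means 1,000 × 1,000 = 1,000,000 backward selections. If that is too many, either count can be reduced, with the choice stated.
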